#### Follow-up

The end of treatment visit will be performed approximately 14 days after the last dose of radiochemotherapy. The end of study visit will be performed 30 days after the surgical intervention. In the event a patient develops any study-related toxicity, he will be followed until its resolution or clinical stabilization.

#### Tumor specimen management

Biopsy fragments will be immediately placed in buffered formalin and allowed to be fixed for 24–48 h. Then, the specimen will be processed overnight for paraffin inclusion. Four-micrometer-thick sections will be obtained from each block, at four levels, and stained with hematoxylin and eosin for histopathological assessment.

The surgical specimen will be delivered to the pathologist fresh and unopened immediately after resection. After inspection and recording of any area of perforation, the non-peritonealized resection margin should be carefully inked. The specimen should then be opened from its anterior surface, excepting the area of the tumor, which should be left unopened to allow for adequate documentation of the circumferential radial margin (CRM). A foam or absorbent paper will then be passed through the residual lumen at the tumor site to aid the penetration of the fixative. The specimen will be allowed to fix in buffered formalin for 24–48 h before further dissection, description, and sampling. The specimen will be sliced transversely at 3–4 mm intervals within a range of 3 cm from the tumor, both proximally and distally. At a minimum, tissue sampling should include four blocks of the tumor, disclosing the deepest level of invasion, involvement of serosal surface or any adjacent organ, and extramural vein invasion; a block from the closest distance of the tumor or extramural deposit or tumor in a lymph node to the non-peritonealized resection margin; a block from the proximal and the distal margins (one each); a block from the transition between the tumor and adjacent normal mucosa; a block from normal mucosa; all lymph nodes identified; any other macroscopic abnormality. If no definite residual tumor can be recognized, the whole scarred area will be blocked for histopathological evaluation. Assessment of pathologic response will be done according to EURECA-CC2 guidelines [49].

#### RAS mutational analysis

Hematoxylin and eosin stained slides will be carefully reviewed by a pathologist to delimit areas with >50 % tumor cells, and adjacent tissue sections will be obtained from formalin-fixed paraffin-embedded tissue for DNA extraction. Specific primers will be used to amplify a 92-bp amplicon of KRAS (exon 2, 3, or 4) or NRAS (exon 2, 3, or 4), which will then be analyzed by high resolution melting (HRM) to screen for mutations. In cases positive by HRM, KRAS exons 2 (codons 12 and 13), 3 (codons 59 and 61), and 4 (codons 117 and 146) and NRAS exons 2 (codons 12 and 13), 3 (codons 59 and 61), and 4 (codons 117 and 146) will be identified by SNaPshot, which is based on the dideoxy single-base extension of an unlabeled oligonucleotide primer. Fragment analyses will be done by capillary electrophoresis. Only patients without KRAS (exon 2, 3, or 4) or NRAS (exon 2, 3, or 4) mutations will be enrolled.

#### Biomarker assessment

EGFR gene amplification and HER-2 gene amplification will be analyzed by fluorescence in situ hybridization on 4-μm thick sections of a representative formalin-fixed paraffin-embedded tissue block. Commercial probes will be used: a test probe that targets EGFR and a control probe for chromosome 7 centromere (CEP7) (Vysis), and a test probe that targets HER-2 and a control probe for chromosome 17 centromere (CEP17) (QBiogene). Slides and probes will be codenatured, and hybridization will take place overnight. After post-hybridization washes, slides will be counterstained with DAPI. Fluorescent images will be sequentially captured with a Cohu 4900 CCD camera, using an automated filter wheel coupled to a Zeiss Axioplan fluorescence microscope and a CytoVision system. Gene amplification will be scored when a ratio EGFR/CEP7 or HER-2/CEP17 is greater than or equal to 2.0 in a minimum of 60 cancer cell nuclei.

EGFR, protein kinase (AKT), and mitogen-activated protein kinase (MAPK) phosphorylation status and Ki-67 will be assessed by immunohistochemical analysis of paraffin-embedded, formalin-fixed tumor tissue. Four-μm sections will be cut and placed in silanized slides. Immunostaining will be performed using a polymer method (BrightVision Poly-HRP-Anti Ms/Rb/Rt IgG, ImmunoLogic, Duiven, The Netherlands). After dewaxing the sections, endogenous peroxidase activity will be inhibited with freshly prepared 0.5 % hydrogen peroxide in distilled water for 20 min. Antigen retrieval will be performed with EDTA buffer, pH 8, for 40 minutes. Incubation with primary antibodies for phosphorylated EGFR (clone Tyr1173 e 53A5), phosphorylated AKT (clone Ser473 e D9E), phosphorylated MAPK (clone Erk1/2,Thr202 e Tyr204), and Ki-67 (clone MIB-1, Dako, Glostrup, Denmark) will be performed overnight at 4 °C, at dilution 1:250, in 1 % bovine serum albumin (BSA) in phosphate-buffered saline (PBS). All incubations will be performed in a humidified chamber. Sections will be developed with a peroxidase substrate solution (0.05 % 3,3-diaminobenzidine tetrahydrochloride, 0.01 % H_2_O_2_ in PBS), counterstained with hematoxylin, dehydrated, and mounted. Appropriate positive and negative controls will be used. Assessment of immunoexpression will be performed by light microscopy at × 400 magnification by a senior pathologist.

### Statistical considerations and quantitative analyses

#### Study endpoints

The primary endpoint is pathologic complete remission (pCR). Pathologic complete remission will be determined on the surgical specimen and defined according to the guidelines recommended by the EURECA-CC2 consensus [2] by a pathologist blinded to the treatment arm.

The secondary endpoint will be the safety profile of the combination lapatinib-capecitabine and radiation therapy in the preoperative setting of patients with resectable rectal cancer assessed by the identification of adverse events and serious adverse events coded with the National Cancer Institute’s Common Terminology Criteria for Adverse Events (CTCAE), version 4.0. An adverse event is defined as any undesirable event associated with the use of a drug, whether or not considered drug related, and includes any side effect, injury, toxicity, or sensitivity reactions, or any undesirable clinical or laboratory event not normally observed in the patient. The following definition of serious adverse event is used: any adverse event that results in death, or is life-threatening, or results in persistent or significant disability or incapacity, requires or prolongs hospitalization, or results in a congenital abnormality or birth defect, or results in any other medically important condition, or an adverse event as a result of an overdose, or is a drug overdose (defined as ≥25 % increase in dose over the protocol-specified dose or more doses are given in a cycle).

Additionally the following exploratory endpoints will be addressed: frequency of and predictive value for the primary endpoint of EGFR amplification status, HER-2/neu amplification status, and predictive value for the primary endpoint of inhibition of EGFR and EGFR downstream proteins on the 14th day of treatment in patients allocated to arm A (MAPK, AKT).

#### Determination of sample size

The trial’s objective is to show the superiority of the lapatinib and capecitabine combination (arm A) over the standard capecitabine (arm B). Thus, the null hypothesis is defined as H_0_: pB ≥ pA, where pA and pB are the probabilities of a pCR for arms A and B, respectively.

The expected sample size calculations were conducted in the context of a Bayesian adaptive randomization design, with stopping rules for early evidence of efficacy/futility and evidence of toxicity. These calculations are based on simulated trial results, which require presetting maximum and minimum total sample size, minimum number of patients fairly randomized to each arm, minimum probability of randomization for each arm, prior distributions for the treatment effect, and stopping rules for efficacy/futility.

We chose a maximum of 80 patients, based on the feasibility of patient’s accrual during the proposed study period. A minimum of 30 patients should be enrolled in the study before stopping the trial due to early evidence of efficacy/inefficacy. However, accrual may stop before the enrollment of 30 patients if there is evidence of toxicity, as defined below. The first 20 patients enrolled in the study will be fairly (non-adaptively) randomized to both arms. During the adaptive randomization phase, the minimum probability of randomization for each arm is set at 0.1.

For arm A, a non-informative prior for treatment effect, i.e., pA ~ Uniform (0,1), and for arm B, a moderate informative prior for treatment effect pB ~ Beta (1.2, 8.8) are used, as shown in Figs. 1 and 2, respectively.

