## Background

Colorectal cancer is the third most incident cancer and the second most common cause of cancer death in Europe [1]. Cancer of the rectum accounts for a third of colorectal cancer cases [2] with 5-year survival rates ranging from 28–55 % in men and 30–64 % in women [3].

Current treatment options for patients with rectal cancer include surgery, radiation therapy, chemotherapy, and targeted systemic therapy. The choice of therapy depends on disease stage, overall health status, and patient preferences. For localized disease, surgical removal of the rectum with total mesorectum excision is the surgical technique of choice, with an estimated overall survival of 86 % and a local recurrence rate of 9 % at 2 years [4]. However, the use of radiotherapy before surgical resection decreases local recurrence rate and impacts overall survival [5]. Moreover, the addition of fluoropyrimidine-based chemotherapy to preoperative radiotherapy further improves local control and pathologic response rates [6]. In patients treated with preoperative radiochemotherapy, whenever downstaging occurs, the risk of death due to cancer is significantly reduced [7]. Despite these therapeutic improvements, patients with localized rectal cancer have 5-year disease-free and overall survival rates of about 59 % and 67 %, respectively [8, 9]. For these patients, development of metastatic disease is the main cause of death.

Capecitabine is a non-cytotoxic fluoropyrimidine carbamate, which functions as an orally administered precursor of the cytotoxic agent 5-fluorouracil. Capecitabine is active as a single agent in colorectal cancer, and it is approved for the adjuvant and palliative treatment of patients with colorectal cancer [10]. Its value as a radiosensitizer in rectal cancer has been established by several phase II trials, with pathologic response rates that range from 7–38 % [11–15]. In a phase III non-inferiority trial, radiochemotherapy with capecitabine was shown to be non-inferior to 5-fluorouracil radiochemotherapy, with survival rates of 76 % at 5 years [16]. Taken together, these data and the more comfortable administration regimen of capecitabine compared to infusional 5-fluorouracil make it the preferential agent for the neoadjuvant treatment of patients with rectal cancer.

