**Fig. 2 Fig2:**
[figure not shown]
Prior distribution for arm B

The trial will be stopped for efficacy if the probability of one arm being superior to the other is greater than 0.95 and for futility if the same probability is less than 0.05. Additionally, the trial stops for futility if the probability of arm A having an effect greater than 0.2 is less than 0.05.

Based on the previous setup, expected sample sizes were computed for three different scenarios, based on 10,000 simulations of trial results:I.pA = 0.30 and pB = 0.12II.pA = 0.25 and pB = 0.12III.pA = 0.12 and pB = 0.12

For scenario I, the expected sample size is 50 with 34 patients enrolled in arm A and 16 in arm B. The probability of choosing arm A as superior is 82 % (equivalent to the power concept in the frequentist framework), and the probability of early stop due to efficacy is 78 %. The expected trial length is 13 months. For scenario II, 56 patients are expected to enroll in the trial with 37 patients in arm A and 29 in arm B. The probability of identifying arm A as superior is 63 % (equivalent to the power concept in the frequentist framework), and the probability of early stop due to efficacy is 64 %. The expected trial length is 15 months. Finally, if no differences exist between the two arms (scenario III), the expected sample size is 60 (30 each arm). The probability of choosing one of the arms as superior is 12 % (equivalent to the probability of type I error in the frequentist framework). The expected trial length is 16 months.

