## Discussion

To our knowledge, this is the first trial to assess the efficacy of dual inhibition of EGFR and HER-2 as a radiosensitizer in resectable rectal cancer. The trial is designed to include an enriched population of patients with KRAS and NRAS wild-type rectal cancer due to evidence of lack of benefit from anti-EGFR strategies in KRAS or NRAS mutated colorectal tumors. However, the role of KRAS or NRAS mutations in localized rectal cancer is uncertain. There is no information on whether this subgroup of rectal cancer patients have a different prognosis compared to patients with activating mutations nor if absence of mutation in KRAS or NRAS is predictive of response to standard radiochemotherapy. Thus, a randomized trial with an active comparator was needed to answer this question. The choice of a randomized adaptive Bayesian design allows an optimized sample size as well as a concurrent comparator. This design optimizes the trial’s sample size and protects eligible patients from randomization to a weakly performing arm, thus improving our ability to decide whether further study of lapatinib in this setting is warranted [50, 51].

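### The 12% type I error is shown only at a pCR of 0.12, the mean of the arm B prior; at higher shared rates arm A is wrongly declared superior in about 25% (pCR 0.20) to 44% (pCR 0.38) of trials

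*Protocol article*

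**What the plan says.** Under *Determination of sample size* the article sets a one-directional null: "the null hypothesis is defined as H_0_: pB ≥ pA, where pA and pB are the probabilities of a pCR for arms A and B". Arm A has a Uniform(0,1) prior, "and for arm B, a moderate informative prior for treatment effect pB ~ Beta (1.2, 8.8) are used". On size and timing it states "We chose a maximum of 80 patients" and "A minimum of 30 patients should be enrolled in the study before stopping the trial due to early evidence of efficacy/inefficacy". The first 20 patients are allocated 1:1. After that, allocation adapts, with a floor of 0.1 per arm.

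The trial stops for efficacy at a posterior probability of superiority above 0.95, and for futility below 0.05 or if P(pA > 0.2) falls below 0.05. *Quantitative analysis* says the probability is calculated continuously once the 30th outcome is known.

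Three scenarios were simulated, all with pB = 0.12. For the only null one, pA = pB = 0.12, the article reports: "The probability of choosing one of the arms as superior is 12" %, and equates this with the type I error.

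Two other statements bear on the control rate. *Background* describes capecitabine as a radiosensitizer "with pathologic response rates that range from 7–38" %. *Discussion* says of RAS wild-type patients: "There is no information on whether this subgroup of rectal cancer patients have a different prognosis", adds that it is also unknown whether wild-type status predicts response to standard treatment, and gives this as the reason for a randomized comparator.

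**The concern.** A type I error has to hold over the null hypothesis, and here that is every pair with pB ≥ pA. The article evaluates it at one point, the one where the arm B prior is centred on the truth. If the true control rate is higher, that prior pulls the arm B estimate down and nothing comparable pulls arm A down. With repeated looks at 0.95, the trial then has many chances to stop for arm A on a difference that comes partly from the prior. Readers told 12% would take a positive result as stronger evidence than it is, and the go/no-go decision on further study of lapatinib rests on that result.

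**Working it through.** **Inputs (all from the article).** Priors Beta(1, 1) for A and Beta(1.2, 8.8) for B; 10:10 run-in; allocation probability kept within 0.1–0.9; looks from 30 to 80 patients; stop at P(pA > pB) > 0.95 or < 0.05, or P(pA > 0.2) < 0.05. The article does not state the exact allocation formula, the outcome lag or the look spacing used in its simulation, so these were varied. The toxicity rule was not simulated.

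**Step 1: what the priors say before any data.** The arm B prior mean is 1.2/(1.2 + 8.8) = 0.12 and its weight is 1.2 + 8.8 = 10 patients. With pA uniform, P(pA > pB) = E(1 − pB) = 1 − 0.12 = 0.88.

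**Step 2: direction of the pull.** Take the scenario I arm sizes (34 and 16) purely as an illustration, with a shared true rate of 0.38. The approximate posterior means are

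- A: (1 + 0.38 × 34)/(2 + 34) = 13.92/36 = 0.39
- B: (1.2 + 0.38 × 16)/(10 + 16) = 7.28/26 = 0.28

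The truth is equal, yet the estimates differ by about 0.11.

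**Step 3: one data set, two decisions.** Suppose 10/25 in A and 3/12 in B. Under the stated priors the posteriors are Beta(11, 16) and Beta(4.2, 17.8), giving P(pA > pB) = 0.956, an efficacy stop. With uniform priors in both arms they are Beta(11, 16) and Beta(4, 10), giving 0.794 and no stop.

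**Step 4: reproduce the plan's figures.** Monte Carlo, 10,000 trials per scenario:

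| Setting | Power I | Power II | Either arm chosen at 0.12 | Expected N, I / II / III |
|---|---|---|---|---|
| Article | 82% | 63% | 12% | 50 / 56 / 60 |
| Allocation by P(pA > pB), no lag, every look | 86% | 70% | 14.4% (A) + 0.5% (B), about 15% | 42 / 49 / 57 |
| Lag 4 patients, looks every 10 | 80.9% | 64.1% | 11.5% | 53 / 59 / 66 |
| Lag 8 patients, looks every 5 | 82.3% | 65.7% | 13.2% | 52 / 59 / 65 |

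No setting matches every figure, but 12% is close to what the design gives at 0.12.

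**Step 5: other points of the null.** Probability that arm A is declared superior when pA = pB (allocation by P(pA > pB), no lag, looks after every outcome; ranges are across independent runs):

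| Shared pCR | Stated priors | Uniform priors in both arms |
|---|---|---|
| 0.07 | 6% | – |
| 0.12 | 14–15% | 5% |
| 0.15 | 19–20% | 8% |
| 0.20 | 25–27% | 11% |
| 0.25 | 31–33% | 12% |
| 0.30 | about 36% | 12% |
| 0.38 | about 44% | 13% |

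On the article's own metric (either arm chosen), the stated design gives about 15% at 0.12, 29% at 0.20 and 49% at 0.38.

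**Step 6: dependence on unstated settings.** At 0.20 / 0.25 / 0.30 / 0.38 the arm A error is 27/31/33/40% with allocation by posterior means, 26/29/33/37% with fixed 1:1, and 25/30/34/42% with a lag of 16 patients. In the settings closest to the article's figures it is 21–24% at 0.20 and 36–41% at 0.38.

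**Step 7: which feature causes it.** Over 0.20–0.38, the unequal priors with a single look at 80 patients give 11–23% (10–14% at fixed 1:1). Continuous looks with uniform priors in both arms give 10–15%. Both together give 25–44%.

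**The case against.** The strongest reply is that this is a phase II trial that openly accepts a lenient error, that an informative control prior is a disclosed design choice, and that the upper rates are unlikely. The cited 7–38% is described as pathologic response, not explicitly as complete response, and 38% is the extreme of several phase II trials. The arm B prior itself puts only 18% of its mass above 0.20 and 2% above 0.38; averaged over that prior, the arm A error is about 14% by interpolation. At 0.07 it is only 6%.

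Much of this stands. The 38% row is an upper bound, and the design is not reckless if the prior is right. But averaging over the prior assumes what is in question, since the article says the rate in RAS wild-type disease is unknown. The excess is also already present just above the prior mean: 19–20% at 0.15.

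Three stronger readings might be inferred and are not supported:

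- **That the 12% is wrong.** It applies to 0.12, where the design gives about 11–15% depending on lag and look spacing, which a condensed article need not report.
- **That prior weight alone produces the excess.** Step 7 shows that neither feature alone reaches 25–44%.
- **That the prior defeats the purpose of the control arm.** Its weight of 10 patients is less than the 16 arm B patients expected even in scenario I, so the concurrent data still count for more.

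**Conclusion.** The point holds as a defect in the stated operating characteristics. Twelve per cent is approximately the type I error at a shared pCR of 0.12 and should not be presented as the type I error of the design. Under the stated rules, wrong selection of arm A rises to about 25–27% at 0.20 and about 44% at 0.38; across the unstated allocation, lag and look settings the ranges are roughly 21–27% and 36–45%.

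This rests on beta-binomial updating, the stated thresholds and looks, no toxicity stop, and treating control rates above 0.12 as possible, as the article does. The article's 12% counts either arm while its null is one-directional, but at 0.12 nearly all of the error is arm A (14.4% against 0.5%), so the comparison is fair. The documents do not show what the control rate will be, so no single false-positive rate can be assigned to the trial.

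**What to change.** 1. Re-run the simulation with null scenarios pA = pB = 0.15, 0.20, 0.25, 0.30 and 0.38. Report wrong selection of arm A and of either arm separately, and state the allocation formula, lag and look spacing used.
2. Replace the single 12% with the resulting range.
3. Prespecify a sensitivity analysis of the final posterior probability of superiority with the same uniform prior in both arms, so that a positive claim that depends on the arm B prior is visible.

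These steps leave the conduct of the trial unchanged. They cost a small amount of simulation work and a less favourable published error rate.

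Changing the decision rule is a separate choice with real costs. Uniform priors in both arms at 0.95 hold the arm A error to about 13% at 0.38, but power falls to roughly 61–68% in scenario I and 45–50% in scenario II. Using Beta(1.2, 8.8) in both arms with a 0.92 cut-off looks attractive because it keeps power near the stated values, but it should not be adopted: its either-arm error is about 16–18% at 0.12 and 34–37% at 0.20, because error moves from arm A to arm B. If the sponsor does change the rule, priors and threshold should be calibrated together over the whole range, on both error measures, with the power loss stated. The trial is open-label and already recruiting, so such a change should be made without reference to accrued outcomes. It would probably need the prior ethics and authority approval that *Ethical considerations* requires for amendments affecting scientific quality.

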**Fig. 1 Fig1:**
[figure not shown]
Prior distribution for arm A

**Fig. 2 Fig2:**
[figure not shown]
Prior distribution for arm B

The trial will be stopped for efficacy if the probability of one arm being superior to the other is greater than 0.95 and for futility if the same probability is less than 0.05. Additionally, the trial stops for futility if the probability of arm A having an effect greater than 0.2 is less than 0.05.

Based on the previous setup, expected sample sizes were computed for three different scenarios, based on 10,000 simulations of trial results:I.pA = 0.30 and pB = 0.12II.pA = 0.25 and pB = 0.12III.pA = 0.12 and pB = 0.12

For scenario I, the expected sample size is 50 with 34 patients enrolled in arm A and 16 in arm B. The probability of choosing arm A as superior is 82 % (equivalent to the power concept in the frequentist framework), and the probability of early stop due to efficacy is 78 %. The expected trial length is 13 months. For scenario II, 56 patients are expected to enroll in the trial with 37 patients in arm A and 29 in arm B. The probability of identifying arm A as superior is 63 % (equivalent to the power concept in the frequentist framework), and the probability of early stop due to efficacy is 64 %. The expected trial length is 15 months. Finally, if no differences exist between the two arms (scenario III), the expected sample size is 60 (30 each arm). The probability of choosing one of the arms as superior is 12 % (equivalent to the probability of type I error in the frequentist framework). The expected trial length is 16 months.

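### Scenario II arm sizes do not sum to the stated total (37 + 29 = 66, not 56); two neighbouring simulation figures also need checking

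*Protocol article*

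**What the plan says.** The figures stand in the Protocol article under the heading on determination of sample size and come from 10,000 simulated trials per scenario.

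- **Scenario I** (pA 0.30, pB 0.12): "the expected sample size is 50 with 34 patients enrolled in arm A and 16 in arm B", length 13 months. On outcome, in per cent: "The probability of choosing arm A as superior is 82" and "the probability of early stop due to efficacy is 78".
- **Scenario II** (pA 0.25, pB 0.12): "56 patients are expected to enroll in the trial with 37 patients in arm A and 29 in arm B", length 15 months. On outcome, in per cent: "The probability of identifying arm A as superior is 63" and "the probability of early stop due to efficacy is 64".
- **Scenario III** (both 0.12): "the expected sample size is 60 (30 each arm"), length 16 months, with a 12% chance of declaring one of the arms superior.

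The same section gives the design inputs: Uniform(0,1) prior for arm A, Beta(1.2, 8.8) prior for arm B, 20 patients randomized equally, a floor of 0.1 on each arm's allocation probability, at least 30 and at most 80 patients. The efficacy stop applies when either arm's probability of superiority passes 0.95. A further futility stop applies when P(pA > 0.2) falls below 0.05. The opening of Methods/design says that allocation after the first 20 patients is weighted by the current success estimates, without a formula.

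**The concern.** The scenario II total and its two arms cannot all be right. In the same scenario, early efficacy stops are printed as more frequent than selection of arm A, although a trial stopped early for arm A is one of the trials that select arm A. In the null scenario the allocation is exactly equal, although the priors are not symmetric and allocation responds to the posterior.

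These are the only expected sizes, power equivalents and error rates in the article. A reader judging how the design performs at the smaller effect has to rely on them, and a misprinted arm size misstates the expected exposure to each treatment.

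**Working it through.** **1. Do the arms sum?** Scenario I: 34 + 16 = 50, as stated. Scenario III: 30 + 30 = 60, as stated. Scenario II: 37 + 29 = 66, against a stated 56. Rounding cannot produce a gap of 10.

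**2. Which scenario II number is out of line?** There are three possible repairs.

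- *Total 66.* Scenario II would then be larger than scenario III (60) yet finish a month sooner (15 against 16 months). Patients per month: 50/13 = 3.85, 56/15 = 3.73, 60/16 = 3.75, but 66/15 = 4.40.
- *Arm A = 56 − 29 = 27.* More patients would be on the worse arm than on the better one, against the purpose of the adaptive allocation.
- *Arm B = 56 − 37 = 19.* Arm A's share is then 37/56 = 66%, close to scenario I (34/50 = 68%). On this reading 29 overstates arm B by 10, or 10/19 = 53%.

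**3. Re-simulation.** This used the stated priors, run-in, floor, limits and stops, with 40,000 trials per scenario. Two inputs are assumptions: allocation in proportion to P(pA>pB), and a fixed number of patients whose outcome is still pending (the lag).

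| Scenario | Stated total (A/B) | Lag 9 | Lag 10 |
|---|---|---|---|
| I | 50 (34/16) | 49.7 (34.0/15.7) | 50.5 (34.7/15.8) |
| II | 56 (37/29) | 55.3 (37.1/18.1) | 56.0 (37.7/18.3) |
| III | 60 (30/30) | 62.3 (36.3/26.0) | 62.8 (36.7/26.1) |

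The settings that reproduce scenario I also reproduce scenario II's total and arm A, with about 18 in arm B.

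**4. 63% against 64%.** Let S be the proportion of trials selecting arm A, and E_A and E_B the proportions stopped early for A and for B. If an early stop for A counts as selecting A, then E_A ≤ S within one set of simulations. All early efficacy stops are therefore at most S + E_B. In scenario II, E_B was about 0.1% (0.3% without the separate futility rule on pA). With E_B = 0.1%, the printed pair needs S between 63.4% and 63.5%, and almost no trial selecting A at its end. Simulated S exceeded all early efficacy stops by 0.04 to 0.2 points with no lag, and by about 2 points at lag 9 (70.2% against 68.1%). Scenario I as printed has S ahead by 82 − 78 = 4 points.

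**5. 30:30 under the null.** With a uniform prior on pA, P(pA>pB) before any data is 1 − E(pB) = 1 − 1.2/10 = 0.88. With equal data:

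- 0/10 in each arm: posterior means 1/12 = 0.083 (A) and 1.2/20 = 0.060 (B); P(pA>pB) = 0.58.
- 1/10 in each arm: posterior means 2/12 = 0.167 and 2.2/20 = 0.110; P(pA>pB) = 0.67.

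Equal results thus still favour arm A. Expected null splits were 32.8:24.8 (no lag), 36.3:26.0 (lag 9), and 29.9:26.9 to 34.0:30.0 under the mildest rule tested, in which the weighting grows with enrolment. Arm A led under every adaptive rule tested with the stated priors, by 3 to 15 patients. With flat priors on both arms at lag 9 the split narrows to 34.5:32.4.

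**The case against.** Only the sum is certain, and it looks like a one-digit misprint in an expected value. No design parameter depends on it. All of that stands.

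A reader might infer that the 63% and 64% contradict each other outright. They do not. The efficacy stop covers either arm while the 63% counts arm A only, and rounding can hide up to a point. Under the null, where stops for B are less rare, either-arm early stops did exceed arm A selection in simulation (14.65 + 0.70 = 15.35% against 14.94% at lag 9). One small scenario I run of 1,500 trials without lag also showed it (86.7% against 86.6%). What remains is that stops for B are negligible in scenario II and that scenario I runs the other way. Another reading is that pending outcomes could overturn an early stop. That could push selection below early stops, but it would reverse scenario I too (about 71% against 83%).

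The re-simulation has limits. The lag of 9 was chosen to match the sizes; the visit schedule and accrual suggest about 12 to 13 pending in arm A, and lag 12 gives totals of 52, 58 and 64. At lag 9 the printed probabilities are missed: arm A selection of about 85% against 82% (I) and 70% against 63% (II), and about 16% against 12% under the null. Toxicity stopping belongs to the design but was left out, because no serious adverse event rate is given. The model therefore cannot show that 63% is wrong.

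Nor can 30:30 be called impossible. The article may leave the allocation formula to the full protocol, and the mildest rule, with long lags, comes within 2 patients of it. That rule, however, gives about 24:20 in scenario I instead of 34:16; no tested rule fits both.

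**Conclusion.** The concern holds as a minor correction with two queries attached.

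- **Certain:** the scenario II arms exceed the stated total by 10. The durations alone favour 56; the re-simulation, under its assumed rule and lag, agrees and puts arm B at about 18 to 19. The sponsor should confirm the value against the original output.
- **Query:** 64% above 63% is not reproduced under the stated inputs, and only rounding could explain it.
- **Query:** the equal null split runs against the direction of the stated priors. That arm A should lead is well supported; by how much depends on the unstated formula.

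It is tempting to conclude that scenario II's size and power cannot both be right, or that feasibility is in doubt. The article does not support either. A total of 56 is compatible with 63% power, and the article ties feasibility to accrual and the maximum of 80. That maximum and the stopping thresholds are untouched.

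**What to change.** Check the archived simulation output, or re-run the simulations with the final priors and rules. Then:

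1. Correct the scenario II arm sizes so that they sum to the total.
2. Restate the 63%/64% pair as the output shows, and say whether the early-stop figure counts either arm or arm A only.
3. Restate the null allocation as the output shows.

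The cost is one check or re-run and a text correction. No change to the design is needed.
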